## Abstract

**Background:**

Geriatric malnutrition in hospitals is common and can be affected by many things, including poor satisfaction toward hospital foodservice. Hospital foodservice plays an important role in a patient’s recovery process by providing adequate nutrients. On top of that, patients’ foodservice satisfaction can easily be afflicted by the quality of food served and the overall foodservice experience. Furthermore, malnutrition can occur from poor foodservice quality, especially among geriatric patients.

**Objective:**

This study aims to assess the effectiveness of the Malaysian Geriatric Patients’ Hospital Foodservice Protocol (MYGERYFS).

**Methods:**

The protocol comprises 3 phases. Phase One is a cross-sectional study that took place at public hospitals with geriatric wards in the Klang Valley. Univariate data from Phase One were analyzed descriptively. Pearson correlation and chi-square were conducted to find factors associated with foodservice satisfaction. Phase Two involves the collaboration of health care professionals in the geriatric field. In Phase Three, a feasibility study will be conducted to determine the feasibility of the MYGERYFS protocol in a hospital among 60 geriatric patients. These patients will be randomized into control and intervention groups, respectively. Intervention care will be done to ensure the safety of the protocol.

**Conclusions:**

This study protocol could potentially benefit the hospital foodservice system and aid in improving geriatric nutritional status.

**Trial Registration:**

ClinicalTrials.gov NCT04858165; https://clinicaltrials.gov/ct2/show/NCT04858165

**International Registered Report Identifier (IRRID):**

RR1-10.2196/42496

## Introduction

“Older people” is defined as individuals aged 65 years or older who are deemed suitable to receive the national pension plan [1]. According to Orimo et al [1], the range of older persons can be divided into two categories. They are (1) “early elderly” (individuals aged 65-74 years) and (2) “late elderly” (individuals aged ≥75 years). In Malaysia, “elderly” is recognized as those aged 60 years and older, due to its policy and program development purposes [2]. The increasing trend of the aging population has shifted the world’s demographic patterns [3]. As a developing country, Malaysia is not spared from this phenomenon [4]. The recent National Health Morbidity Survey (2018) estimated that the country’s older population is at 2.3 million (6.3% of the total population) and is predicted to double within 23 years [2]. The aging process often relates to health complications [2]. Apart from the presence of comorbidities, malnutrition in older people is also common [5].

The reasons for having compromised nutritional status among older individuals are changes in physical, cognitive, psychological, and social factors (eg, living alone), as well as having limited income [6]. Other risk factors include the presence of comorbidities [7,8], poor dental status [9], and inadequate dietary intake [7,10,11]; moreover, those living in health care institutions often complain of having poor foodservice experience [12,13]. Older people with malnutrition often find themselves in a state of dependency, having prolonged hospital stays, an increase in infection rate that eventually diminishes their quality of life, and an increase in health care costs and mortality [6,7,14].

There are countless studies investigating malnutrition among hospitalized older individuals, and the prevalence is indisputable. The global prevalence of malnutrition in hospitalized older patients ranges from 12% to 75% [7]. Consistent with the worldwide trend, Malaysia also shows a prevalence of malnutrition that ranges from 21% to 55% among hospitalized geriatric patients, which appears to be a matter of concern [15].

Despite the interventions carried out thus far, the prevalence of malnutrition among geriatric patients is still appalling [16]. Most older people view themselves as healthy, in spite of their sociodemographic status (educational level, income status, and daily living activities) [17]. Despite their healthy self-image, older individuals are still vulnerable to malnutrition due to their frail condition [6]. In addition, of 52% of malnourished older patients, 18% were found to be nutritionally compromised even before admission [18]. Surprisingly, these older adults even believe that having inadequate nutritional intake is normal without realizing the consequences that malnutrition carries [6].

Hospital meal is considered as one of the important components of care. Hospital meals are served not only to facilitate well-being and recovery but also to contribute to the patients’ satisfactions on their overall treatment experiences [19]. Looking at the hospital foodservice system, oftentimes the patients’ nutritional status is impacted by it. For example, hospital-acquired malnutrition is believed to be caused by the poor quality and appearance of the food and its environment [20]. The same study reported that food quality is found to be the best predictor of patients’ overall satisfaction, followed by service quality given by staff. A study in Australia has proven this by introducing a room service model to hospitalized patients. The results showed good upturns in the patients’ nutritional intake and satisfaction as well as reduced plate waste and patient meal costs after the method was implemented [21].

Another study reported that patients found it tiring to order and eat their food at specific times [22]. On the contrary, these patients were also sensitive to delays and poor service. Further, the study documented that patients appreciated the presence of nonmedical foodservice staff, but at the same time felt pressured by them. According to a study conducted in a military hospital in Turkey, the patients’ satisfaction levels on the hospital’s foodservice system showed inconsistency. The results showed that 51.3% evaluated the foodservice quality to be adequate, while 32.4% deemed it was of inadequate quality. Accordingly, the remaining 16.3% stated that they were uncertain [23]. The different spectrum of thoughts by the patients only makes it hard to fathom, thus affecting the ways of intervention in many hospitals’ foodservice systems. Therefore, the redesigning of hospital foodservice models may be needed not only to drive toward the improvement of patient satisfaction and cost but also to influence clinical outcomes associated with nutritional intake.

Figure 1 shows the conceptual framework of the causes of malnutrition and its possible consequences. This study aims to develop, implement, and evaluate the effectiveness of a Malaysian Geriatric Patients’ Hospital Foodservice Protocol (MYGERYFS) in order to improve both the nutritional status of hospitalized geriatric patients and the quality of the foodservice.

**Figure 1 figure1:**
[figure not shown]
Conceptual framework of the causes of malnutrition and its consequences.

## Methods

### Study Design

The MYGERYFS project is a 2 year and 6 months intervention program, conducted among malnourished older individuals with pre- and postintervention to assess the effectiveness of the protocol. The trial comprises the nutritional status of hospitalized geriatric patients aged 60 years and above in 5 public hospitals in the Klang Valley, which are as follows: (1) Hospital Selayang, (2) Hospital Sungai Buloh, (3) Hospital Kuala Lumpur, (4) Hospital Tengku Ampuan Rahimah, and (5) Hospital Pengajar Universiti Putra Malaysia.

The study comprises the following phases: (1) Phase One—a preliminary study that identified the prevalence and factors associated with hospitalized geriatric malnutrition; (2) Phase Two—protocol development with health care professionals; and (3) Phase Three—testing the feasibility of the protocol. The trial has been registered at ClinicalTrials.gov (NCT04858165) on March 30, 2021.

### Phase One

The first phase of the MYGERYFS is a cross-sectional study conducted to assess the recent nutritional status of older hospitalized patients and the factors associated. Phase One has been completed and analyzed in August 2022. Using the proportion formula by Cochran (1963) [19], a total of 233 geriatric patients were gathered as samples for this study.

In this phase, the patients or their respective caregivers were interviewed by the researchers. A series of questionnaires that hold information on the patients’ sociodemographic and medical background, anthropometry measurements, dietary intake, mealtime barriers, foodservice satisfaction levels, and nutritional statuses were put together. The collected data were assessed and labeled as preliminary data.

### Phase Two

Phase Two of the MYGERYFS protocol studies the current feeding practices and opinions of health care professionals. A group of geriatric health experts, specifically geriatricians, nurses, and dietitians, will be invited to review and discuss the preliminary data. Subsequently, the existing clinical procedures will be audited and improved in line with the recent research. The protocol will be finalized in a consensus meeting.

### Phase Three

The newly developed protocol will be tested in a single institution. Altogether, 60 geriatric patients will be recruited. These patients will be divided into 2 groups (control and intervention groups). The control group patients will be given usual hospital care, and the intervention group patients will be cared for according to the developed protocol for approximately 3 consecutive days. Dietary recall of 3 days was thought to be better than 24-hour recall or 7-day recall [24]. This is because a single 24-hour recall could lead to overestimation of intake, while a dietary recall of more than 3 days often leads to lower intake as respondents feel burdened to report their intake further, thus omitting their food items altogether [24]. Details on their dietary adequacy and clinical outcomes will be documented. The feasibility and safety of the protocol will be evaluated. The findings will provide fundamental data to develop a foodservice protocol for Malaysian geriatric patients.

### Participants

#### Ethics Approval

This study was approved by the National Medical Research Register for Phase One (NMRR-20-308-52632) and was reapplied for Phase Three. In Phase One, a written consent form will be sought from all respondents before the study. Permission from each of the hospitals’ clinical research centers was obtained before data collection.

#### Screening of Nutritional Status

Five public hospitals in the Klang Valley were listed and approached for Phase One of the study. These hospitals were purposely selected due to the availability of their geriatric wards. The selected patients will be screened using the Mini Nutritional Assessment Short Form (MNA-SF). The MNA-SF evaluates 5 components of common geriatric problems, which are food intake, weight status, mobility status, presence of psychological problems, and neurological stress level. These components will be scored based on the patients’ conditions and are categorized into the following: (1) normal nutritional status (12-14 points), (2) at risk of malnutrition (8-11 points), and (3) malnourished (0-7 points) [25].

#### Eligibility and Recruitment

Both Phase One and Phase Three of this study shared similar inclusion and exclusion criteria, as mentioned in Textbox 1.

The summary of the inclusion and exclusion criteria for Phase One and Phase Three of the Malaysian Geriatric Patients’ Hospital Foodservice Protocol (MYGERYFS).
**Inclusion criteria**
Patients aged 60 years and olderAble to understand and speak Malay or English or bothPatients who are on an oral diet or Oral Nutrition Support or bothPatients who are admitted for more than 48 hours
**Exclusion criteria**
Patients with mild dementia or adjustment disorders that are common in geriatric patientsCritically ill patientsPatients who are on full enteral or parenteral feeding

#### Sample Size Calculation

The sample size for Phase One of the study will be calculated using the proportion formula by Cochran (1963) [19]. A total of 233 geriatric patients will be gathered as samples for this study.

Meanwhile, Phase Two will only require the cooperation of health care professionals; thus, no sample size calculation will be calculated.

In Phase Three of the study, 60 geriatric patients will be recruited and divided equally into control and intervention groups. Therefore, a sample of 30 respondents per arm will be required. As suggested by Cohen [25], a sample size of 30 in each arm is needed to detect the differences between groups, which should lead to about a minimum of 80% power in a study.

#### Randomization and Allocation

Patients in Phase Three of the study will be randomized into control and intervention groups, respectively. To do so, patients will be allocated with the help of a computer-generated random number sequence.

### Intervention

Preceding the development of the MYGERYFS protocol, a feasibility study will be conducted during Phase Three. The study will be carried out in a single institution with a total of 60 geriatric patients. These patients will be screened for their eligibility and separated into control and intervention groups, respectively. Those in the control group will receive the usual hospital care, while the other group will experience hospital care according to the developed protocol. Both groups will be observed for their dietary intake for approximately 2 days from the day of the intervention. All of this information will be compared within the 2 groups.

### Outcome Measures

#### Primary Outcome

##### Nutritional Status

The nutritional statuses of geriatric patients were assessed using the MNA-SF. The MNA-SF evaluates 5 components of common geriatric problems, which are food intake, weight status, mobility status, presence of psychological problems, and neurological stress level. These components were scored based on the patients’ conditions and categorized into the following: (1) normal nutritional status (12-14 points), (2) at risk of malnutrition (8-11 points), and (3) malnourished (0-7 points) [25].

##### Foodservice Satisfaction

The patients’ levels of foodservice satisfaction were documented by the validated Acute Care Hospital Foodservice Patient Satisfaction questionnaire by Capra [26] in 2005 via an interviewing method. The questionnaire weighs 4 main foodservice aspects, which are food quality, meal service quality, staff or service issues, and physical environment. The higher the mean score is, the better the results will be [26].

##### Dietary Intake

The amount of food consumed by the respondents in 2 days was recorded and analyzed using Nutritionist Pro (version 2.4.1, First Data Bank) [27]. From these data, the patients’ energy and protein adequacy was compared against their requirements.

#### Secondary Outcomes

##### Anthropometric Measurements

The anthropometric measures considered for this study are as follows:

Body weight was measured using an electronic scale (digital weighing scale; OMRON HBF-357) according to the standard techniques [28].Estimation of weight is done for patients who were unable to stand without assistance using knee height measurement and mid-upper arm circumference. Weight was measured using equations developed by Ross Laboratories [29].Height was measured using a stadiometer (SECA height rod) according to the standard techniques [30].Estimation of height is done for patients with distinctive conditions (eg, kyphosis, scoliosis) using knee height measurement. Height was calculated using equations developed for older Malaysian people [31].BMI was calculated using the following equation: weight in kilograms divided by height in meters squared—weight (kg)/height^2^(m^2^) [30].

##### Mealtime Barriers

The patients’ mealtime barriers were determined and scored using the Mealtime Audit Tool questionnaire. This questionnaire prioritizes the types of potential barriers during mealtime. Each question is marked with a “Yes” or “No” answer. Scoring for this questionnaire is based on the total “No” responses. This value represents the number of barriers faced by the patients. The higher the “No” responses were, the more barriers were experienced [32].

### Statistical Analysis

Data were entered and analyzed using SPSS 25.0 (IBM Corp). In Phase One of the study, descriptive statistics of the continuous data were presented using mean and standard deviation. Meanwhile, categorical data were presented as frequencies and percentages. To analyze the associations of malnutrition, Pearson coefficient correlation and chi-squared test were used. Statistical significance was set at *P*<.05.

In Phase Two, no analysis will be conducted as it only requires the discussion of health care professionals.

In Phase Three, the descriptive statistics will be presented using mean and standard deviation for continuous data. On the other hand, categorical data will be presented as frequencies and percentages. To compare the control and intervention groups, an independent 2-tailed *t* test will be used. Statistical significance is set at *P*<.05.

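### Phase Three compares the arms with an unadjusted t test; for outcomes with a pre-intervention value, ANCOVA on that value would be more precise at almost no cost

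*Protocol article*

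**What the plan says.** All references are to the protocol article.

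- **Statistical Analysis, Phase Three paragraph:** "To compare the control and intervention groups, an independent 2-tailed" *t* test will be used, and "Statistical significance is set at" *P*<.05. No covariate is named. The text does not say whether the test is applied to post-intervention values or to changes.
- **Study Design:** the project is described as one "with pre- and postintervention to assess the effectiveness of the protocol".
- **Screening of Nutritional Status (under Participants, future tense):** "The selected patients will be screened using the Mini Nutritional Assessment Short Form (MNA-SF"). The MNA-SF is also the first of the three primary outcomes; the others are foodservice satisfaction and dietary intake. Weight and BMI are among the secondary outcomes.
- **Intervention:** intake is observed for roughly 2 days once the intervention starts, and then "All of this information will be compared within the 2 groups".
- **Sample Size Calculation:** "60 geriatric patients will be recruited and divided equally into control and intervention groups". The section adds that "a sample size of 30 in each arm is needed to detect the differences between groups" and puts the resulting power at roughly 80% or more. No effect size, SD or dropout rate is given.

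**The concern.** The design is described as pre and post, and a nutritional score is described at screening, yet the one stated analysis gives no role to any value measured before the intervention. A baseline that correlates with the outcome explains part of the between-patient variation. Leaving it out makes the confidence interval wider than it needs to be.

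This matters more in a small trial. The 80% power statement is tied to no effect size, so nothing shows that 30 per arm has power to spare. The article names the method, so this is a stated choice that can be judged as written. The Abstract says Phase Three data are still to be collected, so the choice can still be changed in advance.

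**Working it through.** **Inputs.** From the article: 30 per arm, two-sided 5%, power of about 80% (Sample Size Calculation; Statistical Analysis). Not in the article: the effect size and the baseline-outcome correlation ρ. I take ρ = 0.3, 0.5 and 0.7 as assumptions. No dropout is assumed.

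**The plan's own figure.** The 80% power cannot be reproduced, because no effect size is stated. It can be worked back. The unadjusted *t* test has 58 degrees of freedom and noncentrality d√(n/2) = d√15.

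- Setting power to 80% gives d = 0.736 SD (noncentrality 0.736 × 3.873 = 2.85).
- The normal approximation gives (1.960 + 0.842) × √(2/30) = 0.723 SD.
- At an assumed difference of 0.5 SD the power is 47.8%.

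**ANCOVA on the baseline value.** The residual variance is (1 − ρ²) times the outcome variance, with 57 degrees of freedom. The detectable difference is close to 0.736 × √(1 − ρ²), and 30 per arm acts like 30/(1 − ρ²).

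| Assumed ρ | 1 − ρ² | Detectable difference at 80% power (SD) | 30 per arm acts like | Power at 0.5 SD |
|---|---|---|---|---|
| none (*t* test) | 1.00 | 0.736 | 30 | 47.8% |
| 0.3 | 0.91 | 0.702 | 33 | 51.4% |
| 0.5 | 0.75 | 0.637 | 40 | 59.4% |
| 0.7 | 0.51 | 0.525 | 59 | 76.0% |

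**If the *t* test is meant for change scores.** With equal variances before and after, a change score has variance 2(1 − ρ) relative to the post value: 1.40, 1.00 and 0.60 at the three correlations. The ANCOVA figures are 0.91, 0.75 and 0.51. The gap is 2(1 − ρ) − (1 − ρ²) = (1 − ρ)², which is never negative. So, apart from the one degree of freedom, ANCOVA does at least as well on either reading.

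**Which outcomes could have a baseline.**

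- *MNA-SF points score:* yes, if the described screening is done at entry to Phase Three.
- *Weight and BMI:* yes, if measured at entry. The article does not say.
- *Dietary intake:* none described; observation begins with the intervention.
- *Foodservice satisfaction:* none described.

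For the last two, the only available covariate would be the screening MNA-SF score. The article's one result linking nutritional status to satisfaction is not significant (Phase One chi-square 12.778 on 8 df, *P*=.12), so it gives no reason to expect a large gain there.

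**The case against.** The strongest reply is that nothing is wrong with the *t* test. Patients are randomised, so it is unbiased, holds its error rate, and has a standard error that already allows for chance imbalance. That stands. A reader might infer that the planned analysis is biased or invalid, and the article does not support this. The loss is one of precision only.

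The second reply is that the baseline is not clearly there. The pre and post wording covers the whole project. The screening section opens with the five Phase One hospitals, the eligibility list does not mention the MNA-SF, and the Intervention section speaks of eligibility screening without naming a tool. This stands as a limit: the gain applies only to outcomes actually measured before the intervention, and at ρ = 0.3 it is small.

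Two stronger readings are tempting:

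- *That a t test will be run on categories.* The article says only that categorical data will be shown as frequencies and percentages. The MNA-SF points, satisfaction score and intake can all be compared as continuous. That no test is named for categories is detail an article may leave to the full plan.
- *That within-arm changes will be tested.* The word *within* in the Intervention section could suggest it, but the stated test is an independent one between control and intervention, and no paired test appears anywhere. This is a wording slip.

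**Conclusion.** The point holds as an inexpensive improvement to a valid analysis. For a continuous outcome with a pre-intervention value, ANCOVA lowers the difference detectable at 80% power from 0.74 SD to 0.70, 0.64 or 0.53 SD at correlations of 0.3, 0.5 and 0.7. The size rests wholly on those assumed correlations and on the baseline being recorded in Phase Three.

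The gain should not be read across to all three primary outcomes. It is best supported for the MNA-SF points score and possible for weight and BMI. On what the article describes, it may be small or nil for intake and satisfaction.

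**What to change.** 1. For each continuous Phase Three outcome with a pre-intervention value, replace the *t* test with ANCOVA of the post value on arm and that baseline. Report the adjusted between-group difference with its 95% confidence interval.
2. Enter each baseline once. For the MNA-SF, the screening score is the baseline and should not also be added as a separate covariate.
3. State which outcomes are measured before the intervention, and confirm that the MNA-SF is scored at entry to Phase Three.
4. For outcomes with no baseline (intake, and satisfaction if not taken beforehand), keep the between-group comparison. Adjustment for the screening MNA-SF score is optional.
5. In the Intervention section, change *within* to *between* the 2 groups, as a correction of wording only.

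I would not require covariate-adjusted logistic or ordinal models for the categories. If Phase Three resembled Phase One, 17.2% malnourished would be about 0.172 × 30 ≈ 5 patients per arm, which may be too few to support them.

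The cost is a few lines of text and one degree of freedom per covariate. No extra patients are needed, and no extra measurements where the baseline is already taken.
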